### Statistical analysis

Per protocol and Intention-to-treat (ITT) analyses will be performed, following the CONSORT and CONSORT-eHealth recommendations [56, 83]. Between-group differences in baseline clinical and socio-demographic characteristics will be explored using analysis of variance (ANOVA) for continuous data, and chi-square tests (χ2) for categorical variables. Both normality and multinormality assumptions will be assessed by applying the Kolmogorov-Smirnov (K-S) test, skewness and kurtosis indexes, and histogram and Q-Q plots. Levene’s test will be conducted to check homoscedasticity assumptions for equality of variances, and Mauchly’s test to explore sphericity assumptions. Missing data patterns will be assessed, and whether missing data are missing completely at random (MCAR) will be checked with Little’s MCAR test [84]. The ITT principle will be applied for primary and secondary outcomes collected at post-treatment, and at the 3, 6, and 12-month follow-ups. In this regard, the maximum likelihood (ML) method using the Expectation Maximization (EM) algorithm will be used to deal with missing data, due to its flexibility in repeated-measures ANOVAs in handling missing data appropriately (i.e., [85, 86]. Nevertheless, several approaches will also be considered and assessed using sensitivity analyses in order to apply the most robust and adequate method based on both missing data patterns and literature recommendations (i.e., [87, 88]. Repeated analysis of variance (rm-ANOVA) will be performed to explore the main and interaction effects of the treatments on all the primary and secondary outcomes. Significant effects will be followed up by pairwise comparisons, such as the Tukey procedure when the homoscedasticity assumption is met, and the Games-Howell procedure if this assumption is not met. Effect sizes (Cohen’s *d*) and their respective 95% confidence intervals (95% IC) will be calculated and reported for within- and between-group comparisons, according to authors’ recommendations [89–91]. In addition to ITT analyses, per protocol analyses will also be conducted. It is true that these analyses suffer from selection bias, but they will allow us to reach conclusions about the efficacy of the treatment in patients who complete all the intervention modules [92].

For acceptability and usability measures, data analysis will be based on completers. Separate multivariate analysis of variance (MANOVA) for expectations, satisfaction, and usability will be performed, where all items are entered into the MANOVA as dependent variables, and the experimental group as a fixed factor (independent variable).

Finally, multiple regression analysis and mediation analysis will be conducted to explore potential predictors and mediators of depressive symptoms. Mediation analyses will be performed through bootstrap regression analysis using the Preacher and Hayes (2004) approach. All statistical analyses will be conducted using IBM SPSS Statistics for Windows, version 23.

We will review the state of the art analytical methodology for RCT before performing the analyses of the data, in order to use the best statistical analysis procedure. Thus, there may be some variations in the statistical analysis procedures.

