In sum, this study has several strengths. To the best of our knowledge, this is the first randomized dismantling intervention study for depression with the aim of exploring the contribution of a PPs component and the BA component in an Internet-based intervention. The three protocols are online interventions, helping to reach many people who need psychological treatments and would not otherwise have access to them. Furthermore, acceptability and usability measures will be included in order to assess the intervention’s feasibility and acceptance, in addition to an efficacy study. Finally, potential mediator mechanisms will be explored to identify the variables that lead to changes in depressive symptoms.

We are aware that this study has limitations. One of them is that the number of BA and PPs modules in the *IBAc* and *IPPc* is higher than in the *IGc*, although the clinical content is the same in the global protocol and in the protocols for the BA and PPs components. The reason for this is that the three protocols contain the same total number of modules (8 modules per each) and a similar number of words. We give all the patients the same amount of time to do the intervention to try to control this. Another limitation is that the dropout rates are expected to be high (around 30%) [103]. Efforts will be made to minimize the dropout rates by providing ICT and human support. Approaches to handling missing data will be considered and assessed using sensitivity analyses in order to apply the most robust and adequate method, based on both the missing data patterns and recommendations found in the literature (i.e., [87, 88]. In addition, difficulties in the recruitment phase will be considered.

In summary, this study extends the current literature about Internet-based interventions for depression. If positive results are achieved, they may have an important impact by providing better knowledge about the core elements of evidence-based treatments for depression.

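### EM completion followed by repeated-measures ANOVA most likely treats predicted scores as observed, which dilutes arm differences or inflates false positives, and the primary missing-data method is not fixed in advance

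*Protocol article*

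**What the plan says.** All of this stands in the protocol article, section Statistical analysis, unless noted.

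- For primary and secondary outcomes under intention to treat, "the maximum likelihood (ML) method using the Expectation Maximization (EM) algorithm will be used to deal with missing data". The reason given is "due to its flexibility in repeated-measures ANOVAs in handling missing data appropriately".
- The test itself: "Repeated analysis of variance (rm-ANOVA) will be performed to explore the main and interaction effects of the treatments". Cohen's d with 95% confidence intervals is promised for within- and between-group comparisons.
- Software: "All statistical analyses will be conducted using IBM SPSS Statistics for Windows, version 23".
- The method is then reopened: "several approaches will also be considered and assessed using sensitivity analyses in order to apply the most robust and adequate method", the choice being "based on both missing data patterns and literature recommendations". The limitations paragraph of the Discussion repeats this.
- The section closes with a review of current methodology, to take place before the analyses, and the remark that "there may be some variations in the statistical analysis procedures".
- Dropout is put at 30% in the sample size section and at around 30% in the Discussion.

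No mixed model, multiple imputation or rule for pooling estimates is named.

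**The concern.** EM is chosen here because it serves rm-ANOVA. Since rm-ANOVA drops any participant with a gap, EM can help it in practice only by supplying the missing scores. If that is done once and the completed table is analysed as 192 observed participants, the analysis ignores that part of the data are predictions. Two different errors follow:

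- **Arm not in the EM model.** Dropouts from every arm are given the pooled response, so arms are pulled towards each other.
- **EM run within arm, or with arm indicators.** The arm contrast is about right, but the predicted values carry no residual scatter and count as full information. The error term is too small and the F test rejects too often.

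This matters more than usual in this trial. Three active arms are compared, and the design assumes that the interaction explains only 1% of variance. Dilution could hide what a component contributes; an undersized error term could invent a contribution.

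The second strand is that a sensitivity analysis should challenge a primary analysis that is already fixed. Here it serves to find one.

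**Working it through.** **Inputs from the protocol article.** Three arms of 64, alpha 5%, correlation ρ = 0.7, sphericity, explained variance 0.01, dropout about 30%, five occasions (pre, post, 3, 6 and 12 months).

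**Assumptions the article does not settle.** Whether arm enters the EM model, when dropouts leave, and that loss is random. Scores are scaled to SD 1.

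**1. The plan's own figure.** f² = 0.01/0.99 = 0.0101. With m occasions, λ = N·m·f²/(1−ρ). For N = 147 and m = 2, λ = 147 × 2 × 0.0101/0.3 = 9.90 on 2 and 144 df, which gives power 0.803. So 147 is reproduced, with two occasions (five would give 92-93). Then 147 × 1.3 = 191.1, rounded up to 192. If one arm departs from the other two by δ after treatment, f² = (2/9)(1/4)δ² = δ²/18, so the planned effect corresponds to δ = √(18 × 0.0101) = 0.426 SD.

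**2. Arm left out of EM, fraction p losing all post-baseline data.** The filled arm mean is about (1−p)·(arm mean) + p·(pooled mean), so the arm difference becomes (1−p)·δ = 0.7 × 0.426 = 0.298. Simulation gave 0.296. Across repeat simulations the loss was 23-33%, with type I error at 5-6%.

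**3. EM within arm, two occasions.**
- Change-score variance that the ANOVA sees: (1−p)·2(1−ρ) + p(1−ρ)² = 0.7 × 0.6 + 0.3 × 0.09 = 0.447.
- Actual variance of the arm mean change, times 64: (1−ρ²)/(1−p) + (1−ρ)² = 0.51/0.7 + 0.09 = 0.819.
- Ratio 0.819/0.447 = 1.83. The 5% critical value of F(2,189) is 3.04, so the test in effect rejects at 3.04/1.83 = 1.66, which has probability 19%. Simulation: 19-21%.
- Coverage of a nominal 95% interval: 1.96/√1.83 = 1.45, or about 85%. Simulation: about 84%.

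**4. EM within arm, five occasions in one test.** The mean of the four later scores has variance (1 + 3 × 0.7)/4 = 0.775. Averaged over the four within-person contrasts:
- Seen by the ANOVA: [0.7 × 4 × 0.3 + 0.3 × 0.8 × 0.09]/4 = 0.215.
- Actual: [0.8 × (0.775 − 0.49)/0.7 + 0.8 × 0.09 + 3 × 0.3/0.7]/4 = 0.421.
- Ratio 1.95. The critical value of F(8,756) is 1.95, so the effective cut-off is 1.00, which has probability 44%. Simulation: 42-45%.

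**5. How the figures move (simulation, 64 per arm, ρ = 0.7).**

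| Missing data | Arm left out: loss of arm difference | EM within arm: type I error |
|---|---|---|
| 30% lose all post-baseline data | 23-33% | 19-21% (2 occasions), 42-45% (5) |
| Gradual, reaching 30% at 12 months, 5 occasions | 16-17% at 12 months | 24-25% |
| 20% lose all post-baseline data | 17-22% | 13% (2), 27% (5) |
| 10% lose all post-baseline data | 10-14% | 7% (2), 12% (5) |

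With autoregressive correlation and a Greenhouse-Geisser correction at 30%, the within-arm error was 18-32%. Adding random residual noise to a single fill does not cure the problem: with all post-baseline data lost, the pooled estimate was still 0.29-0.30 and the within-arm type I error 15% (two occasions) and 32% (five).

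**6. Comparator.** A direct-likelihood mixed model on the observed data gave a type I error of 4.9% (two occasions), 4.5% (five, all post-baseline data lost) and 4.2% (five, gradual loss). It recovered a true difference of 0.40 as 0.40 when all post-baseline data were lost.

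**The case against.** The best defence is that the article never says values are filled once. EM is also a way to obtain likelihood estimates without analysing filled data, and whether arm enters the model is a detail that an unseen analysis plan may settle. This stands in part: single filling is an inference, and which of the two harms applies is open. The inference is still the natural one, because EM is justified by its use in rm-ANOVA and no other route from EM to the test is described. It is a stated method choice, not an omitted detail.

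The figures also depend on the scenario. A reader might take a 44% false-positive rate, or a 30% loss of effect, as a property of this trial. The article gives a dropout rate but not its timing, so it does not support that. Those values need 30% of participants to provide nothing after baseline, and the 44% also needs all five occasions in one test. If arm is left out, type I error stays near 5% and the harm is dilution alone.

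Finally, a reader might infer that the method will be chosen after the results are seen. The text does not say so. It bases the choice on missing-data patterns and the literature, and puts the methods review before the analyses. What remains is narrower: approaches are compared through sensitivity analyses in order to pick one, and nothing requires that pick to precede comparison by arm.

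**Conclusion.** The point holds in conditional form. On the likeliest reading, neither way of running EM gives a sound primary analysis at the dropout the protocol itself expects: one loses roughly a sixth to a third of the arm difference, and the other raises a nominal 5% test to roughly 20-45%. At 10-20% loss the ranges are 10-22% shrinkage and 7-27% type I error. Confidence intervals are affected under both.

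These sizes rest on a single completed data set, 64 per arm, correlation 0.7 and loss that is random, and they move with the timing of dropout as tabulated. The charge on the choice of method is that it is not fixed in advance, not that it will follow the results.

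**What to change.** Make the primary intention-to-treat analysis one of the following, and name which:

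- a likelihood-based linear mixed model on all observed scores, with arm, occasion and arm by occasion, and no imputed values. The MIXED procedure in SPSS fits it, so the software need not change; or
- multiple imputation with arm in the imputation model, with estimates and standard errors pooled by Rubin's rules.

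State the choice before any comparison by arm. Reword the sentences in Statistical analysis and the Discussion so that other missing-data approaches are sensitivity analyses only and do not decide the primary method. Limit the closing remark on variations to changes that are documented before that comparison.

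The cost is a change of wording and modest extra analysis work; no new data are needed. Compared with within-arm single filling, the confidence intervals will be wider, because they then reflect the information actually collected.

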## Methods/design

### Study design

The current study will be a three-armed, simple-blinded, randomized controlled clinical trial with a dismantling design. Specifically, three groups will be compared: a) an Internet-based Global Protocol condition (IGc), b) an Internet-based BA Protocol condition (IBAc), and c) an Internet-based PPs Protocol condition (IPPc). At this moment, the study is ongoing, and we are in the participant recruitment phase. Participants will be randomly allocated to one of the three experimental conditions.

Randomization will be stratified by levels of depression severity (mild to moderate).

We will carry out block randomization within each stratum to certify that all levels of depression are balanced across the three experimental conditions. The study follows the CONSORT statement (Consolidated Standards of Reporting Trials) [54, 55], CONSORT-EHEALTH [56] and SPIRIT guidelines (Standard Protocol Items: Recommendations for Interventional Trials) [57, 58]. Participants’ assessments will be performed at pre-treatment and post-treatment. Furthermore, there will be three follow-ups: at 3, 6, and 12 months. Figure 1 shows the study flowchart.

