### Participants, recruitment and eligibility criteria

The RCT will be carried out at the Emotional Disorder Clinic in Universitat Jaume I. Participants will be adult volunteers with mild to moderate depressive symptoms (from 14 to 28 on the Beck Depression Inventory-II, BDI-II) [59].

Participants will be recruited through the website specially developed for this aim, emails, phone calls, or personal visits, and they will be attended to by a clinician. Once a potential participant has been identified by the clinical psychologist, s/he will be informed about all the characteristics of the study. Any questions or doubts will be clarified in order to ensure that participants have understood all the information correctly. Those who are interested in participating will sign the informed consent. Furthermore, an independent researcher will assess whether they meet all the inclusion criteria.

To participate in the study, participants must meet these inclusion and exclusion criteria. The inclusion criteria are: a) 18 to 65 years old; b) able to read and understand Spanish; c) access to Internet; d) knowing how to use the Internet; and e) experiencing mild to moderate depressive symptoms (from 14 to 28 on the Beck Depression Inventory-II [BDI-II]). Exclusion criteria include: a) receiving a psychological intervention; b) suffering from a severe Axis I mental disorder: alcohol and/or substance dependence disorder, bipolar disorder, psychotic disorder, or dementia; c) having ideation or a significant plan for suicide (assessed by the MINI and item 9 of the BDI-II). Receiving pharmacological medication while participating in the study is not an exclusion criterion. However if the patient has an increase in the pharmacological treatment, s/he will be excluded from the study analysis. Nevertheless, a reduction in the medication does not imply exclusion from the study. We will offer alternative treatments to the participants who do not meet the criteria for the present study.

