**Sample size and power calculations**

The a priori sample size determination was performed based on the main objective of this investigation. Following Cohen’s (1988) guidelines, we assumed a proportion of explained variance of low magnitude for the interaction between the type of intervention and the measurement occasion, that is, 0.01. For a significance level of 5%, statistical power of 80%, assumed sphericity, and correlation of .7 between repeated measures (following Rosenthal’s 1991 recommendation), the total sample size needed was 147 participants (49 per intervention group). To this figure, an additional 30% was added to anticipate potential dropouts. Therefore, the total sample size of the study was 192 participants (64 per intervention group). Sample size calculations were carried out with the statistical program G*Power 3.1.9.2 [82].

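### The planned rm-ANOVA names no baseline covariate and no severity stratum: it is valid, but at the protocol's own correlation baseline adjustment would cut variance by about 15%, probably by less for the BDI-II

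*Protocol article*

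**What the plan says.** All references are to the protocol article.

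- **Model** (Statistical analysis): "Repeated analysis of variance (rm-ANOVA) will be performed to explore the main and interaction effects of the treatments"; this applies to every primary and secondary outcome. Where an effect is significant, Tukey or Games-Howell pairwise comparisons follow. No covariate and no stratum factor is named. The section does not say outright that baseline is one of the repeated occasions.
- **Randomisation** (Study design): "Randomization will be stratified by levels of depression severity (mild to moderate", with blocks inside each stratum.
- **Sample size** (Sample size and power calculations): the effect is a "proportion of explained variance of low magnitude for the interaction between the type of intervention and the measurement occasion, that is, 0.01". The other inputs are "For a significance level of 5%, statistical power of 80%, assumed sphericity, and correlation of .7 between repeated measures", and the result is that "the total sample size needed was 147 participants (49 per intervention group" before 30% is added for dropout, giving 192.
- **Entry range** (Participants, recruitment and eligibility criteria): "experiencing mild to moderate depressive symptoms (from 14 to 28 on the Beck Depression Inventory-II [BDI-II".
- **Reservation** (end of Statistical analysis): the methods may still change after a review of current methodology. No alternative model is named.

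**The concern.** If the pre-treatment score is one level of the repeated factor, a two-occasion group-by-time test is the same as an ANOVA of change scores. A change score subtracts the whole baseline value, whereas regression on baseline subtracts only the part that predicts the outcome. Under randomisation both estimate the same difference, but the regression has the smaller residual variance unless its slope happens to equal 1. The severity stratum, which the design uses, is also absent from the model.

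The second issue is the group main effect. Averaged over occasions that include baseline, it mixes in a time point at which no treatment effect can exist. Pairwise comparisons on those averages shrink the difference being tested. In a dismantling trial the pairwise contrasts (full programme against each reduced programme) are the scientific question, so lost power there matters most.

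**Working it through.** **Inputs from the protocol.** Three arms; explained variance 0.01, so f² = 0.01/0.99 = 0.0101; alpha 0.05; power 0.80; rho = 0.7; sphericity; 147 needed; 192 recruited; 30% dropout.

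**1. Reproduce 147.** For the within-between interaction with N participants and m occasions, lambda = f²·N·m/(1−rho), with df1 = 2(m−1) and df2 = (N−3)(m−1).

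| m | Smallest N for 80% power | Rounded to equal arms |
|---|---|---|
| 2 | 147 | 147 |
| 3 | 121 | 123 |
| 4 | 104 | 105 |
| 5 | 92 | 93 |

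Only m = 2 gives 147: lambda = 0.0101 × 147 × 2/0.3 = 9.90, power 0.803. The calculation is therefore a pre/post test, which equals a change-score ANOVA.

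**2. Gain from baseline adjustment, equal standard deviations.** In units of the common variance, a change score has variance 2(1−rho) and the baseline-adjusted outcome has 1−rho². The ratio is (1+rho)/2 = 1.7/2 = 0.85. Variance falls by 15%; since √0.85 = 0.922, the standard error falls by 7.8%. Dividing lambda by 0.85 and using one more degree of freedom:

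| Evaluable N | Change score | Baseline-adjusted |
|---|---|---|
| 147 | 0.803 | 0.866 |
| 134 (192 × 0.7) | 0.762 | 0.830 |

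The N needed for 80% power falls from 147 to 125 (126 for equal arms).

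**3. Unequal standard deviations.** With s = SD after / SD before, the ratio becomes s²(1−rho²)/(1+s²−2·rho·s). At rho = 0.7 it is 0.850 for s = 1, 0.981 for s = 1.25 and 0.998 for s = 1.5. The 15% depends on s being close to 1.

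**4. What the BDI-II entry range does.** The protocol gives no standard deviations, so this is an illustration. Assume an unselected normal population with mean 18–25, SD 8–10 and rho = 0.7, then select baseline scores of 14–28. Selection leaves the slope (0.7) and the residual variance (0.51·SD²) unchanged but shrinks the baseline variance. The observed rho falls to about 0.36–0.43, s rises to about 1.65–1.97, and the variance ratio is 0.96–0.97, a gain of about 3–4%. For example, with mean 20 and SD 10 the selected baseline SD is about 3.9, so the ratio is 51/(0.09 × 3.9² + 51) = 51/52.4 = 0.97. The PANAS is not truncated directly, so its gain could be nearer 15%. On the same illustration, with an assumed cut at 20, adding only the stratum to the change-score analysis gains about 2–3%.

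**5. Pairwise tests, if run on means over all five occasions.** This use of Tukey is inferred. Take one arm differing by d at every post-randomisation occasion. Matching f² for two occasions gives d² = 18·f² = 0.182, so d = 0.426. Assume rho = 0.7 between all occasions and 45–49 per arm.
- Five-occasion mean: difference 0.8 × 0.426 = 0.341; variance (1 + 4 × 0.7)/5 = 0.76; noncentrality 0.341/√0.76 × √(n/2) = 1.86 to 1.94, against a Tukey critical value of about 2.37. Power is about 0.31 to 0.34.
- Baseline-adjusted contrast at post-treatment: difference 0.426; variance 1 − 0.49 = 0.51; noncentrality 2.83 to 2.96, same critical value. Power is about 0.68 to 0.72.

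**The case against.** The strongest defence is that nothing here is an error. The group-by-time interaction is a valid test under randomisation, and the sample size uses the same family of test, so the plan and its power calculation agree. Baseline as an occasion is an inference, although the pre/post reproduction of 147 and the planned within-group effect sizes make it the natural reading. The article does not say which means the Tukey or Games-Howell tests compare. Covariates are often left to an analysis plan, and the article reserves the right to change its methods. All of this stands, and it makes the point a recommendation on efficiency. It does not remove the point: the article does name a model for every primary and secondary outcome, and the reservation names no better one.

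Two stronger readings are tempting and should be resisted.

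- A reader might infer that the 14–28 entry range lowers the correlation and so pushes the loss well above 15%. The ratio (1+rho)/2 holds only for equal standard deviations, and truncating baseline breaks that condition. The same selection that lowers rho raises the ratio of standard deviations, and the gain on the BDI-II shrinks to a few percent. The only correlation the protocol gives is 0.7.
- A reader might infer that leaving out the stratum invalidates the test. It tends to make standard errors slightly too large, so the error is on the conservative side. The stratum is also a coarse form of baseline severity and adds little once the continuous BDI-II baseline is in the model.

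**Conclusion.** The point holds as a modest, inexpensive gain in efficiency. The planned analysis names neither baseline nor stratum, and the test on which the trial was sized is an unadjusted change-score comparison. The 15% variance reduction rests on the protocol's rho of 0.7 and on equal standard deviations before and after treatment; it is a plausible figure for the PANAS and probably too high for the BDI-II. The power figure at 134 further assumes that 30% of the 192 contribute no outcome.

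The dilution of pairwise comparisons could cost more (about a third power against roughly 70%), but only if those comparisons use group means averaged over occasions that include baseline. The article leaves that open.

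**What to change.** State one model for each continuous outcome measured at these visits. The dependent values are those at post-treatment and 3, 6 and 12 months; the terms are arm, occasion, arm by occasion, the outcome's own baseline score and the randomisation stratum. Take the pairwise arm contrasts from the adjusted means of that model. Do not interpret a treatment main effect that averages in the pre-treatment score, and say which means the multiplicity-adjusted comparisons use.

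If the gain is quoted, give it as about 15% of variance at rho 0.7 with equal standard deviations, and less for the BDI-II if they differ.

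The cost is a change of wording, one or two degrees of freedom, and the assumption of a linear baseline slope. No new data and no further recruitment are needed.

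### The pairwise tests after a significant effect are not tied to the arm-by-occasion contrast on which the trial is powered

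*Protocol article*

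**What the plan says.** The Sample size and power calculations section assumes a "proportion of explained variance of low magnitude for the interaction between the type of intervention and the measurement occasion, that is, 0.01". It continues: "For a significance level of 5%, statistical power of 80%, assumed sphericity, and correlation of .7 between repeated measures", and concludes that "the total sample size needed was 147 participants (49 per intervention group"). The interaction is therefore the effect on which the trial is sized.

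The Statistical analysis section plans a repeated-measures ANOVA for main and interaction effects on all primary and secondary outcomes. It then says: "Significant effects will be followed up by pairwise comparisons, such as the Tukey procedure when the homoscedasticity assumption is met". For unequal variances the same sentence gives the alternative: "and the Games-Howell procedure if this assumption is not met". The choice between the two procedures depends only on homogeneity of variance. The section does not say whether the tests compare arm means averaged over occasions, arm means at each occasion, or changes from baseline. Mauchly's test of sphericity is planned, but no follow-up procedure is linked to it. Cohen's d with 95% confidence intervals is promised within and between groups, without saying whether the between-group d refers to change or to raw scores. The section ends by allowing the statistical procedures to vary.

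**The concern.** With three arms, a significant interaction F-test says only that the arms do not all change alike. Which component matters (the global protocol against the one without positive strategies, or against the one without behavioral activation) is decided by the pairwise step, so that step carries the dismantling question.

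Tukey and Games-Howell are procedures for independent groups. In a repeated-measures ANOVA the only factor with independent levels is arm, so the literal application compares arm means averaged over all occasions, baseline included. That is not the quantity behind the interaction. A second application, raw scores at each occasion, estimates the arm effect without bias under randomization but does not use each participant's baseline. A third, change scores, matches the interaction. The text permits all three, and the answer about a component can turn on which one is picked at analysis. This is separate from how to adjust for multiple pairs.

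**Working it through.** **Inputs** (Sample size and power calculations): alpha 0.05, power 0.80, sphericity, r = .7, explained variance 0.01, three equal arms. The number of occasions in the calculation is not stated; five are planned.

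**1. The plan's own figure.** f² = 0.01/0.99 = 0.0101, so f = 0.1005. For the within-between interaction, λ = f²·N·m/(1 − r), with df1 = (3 − 1)(m − 1) and df2 = (N − 3)(m − 1). With m = 2 and N = 147, λ = 0.0101 × 147 × 2/0.3 = 9.90 on 2 and 144 df, and power is 0.803. The stated 147 is reproduced exactly. With m = 3, 4 or 5 the same formula gives 123, 105 or 93, so the calculation fits two occasions. Then 147 × 1.3 = 191.1, rounded up to 192 for equal arms.

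**2. The difference this effect implies.** Take SD 1 at each occasion and let one arm differ from the other two by D at post-treatment only. The interaction residuals have mean square D²/18, so D = √(18 × 0.0101) = 0.426.

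**3. The same difference under three comparisons** (49 per arm; Tukey critical value 3.349/√2 = 2.368):

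| Compared | Difference | SD | Standardized | Power for one true pair |
|---|---|---|---|---|
| Mean of two occasions | D/2 = 0.213 | √((1 + .7)/2) = 0.922 | 0.231 | 11% |
| Raw post-treatment | 0.426 | 1 | 0.426 | 40% |
| Change | 0.426 | √(2(1 − .7)) = 0.775 | 0.550 | 64% |

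With equal variances, the mean of two occasions is uncorrelated with their difference: Cov(pre + post, post − pre) = Var(post) − Var(pre) = 0. A significant interaction therefore makes a significant pair on averaged means no more likely.

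**4. Significant interactions with no arm pair found** (simulation, compound symmetry, no missing data, Tukey at 5%):

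| Compared, two occasions | 49 per arm | 64 per arm |
|---|---|---|
| Averaged over occasions | about 80% | about 75% |
| Raw post-treatment | about 39% | 28% to 29% |
| Change | about 2% | about 1% |

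| Compared, five occasions | 49 per arm | 64 per arm |
|---|---|---|
| Averaged over occasions | 31% to 62% | 19% to 50% |
| Any occasion, each at 5% | 6% to 10% | 2% to 4% |
| Any change from baseline, each at 5% | under 1% | under 1% |

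The five-occasion ranges cover four illustrative patterns: one arm better from post-treatment on, three arms spread apart, a gap that grows, and a gap that fades. Each is scaled to f = 0.1005. With Bonferroni over the occasions, the any-occasion comparison misses 21% to 29% at 49 per arm. With Bonferroni over the four changes, the change comparison misses at most about 3%.

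**5. Occasion comparisons, only if an independent-groups error were used.** The standard error would be too large by 1/√(1 − .7) = 1.83. A nominal two-sided 5% test would then have a true level of about 0.03%, because 1.96 × 1.83 = 3.58. The error is conservative.

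**The case against.** The strongest reply is that the sentence is underspecified rather than wrong. The arms are independent groups, so Tukey or Games-Howell on change scores is perfectly valid, and nothing in the text rules it out. A reader might infer that these procedures cannot test arm differences in change; that is not so, and the 2% figure above comes from Tukey's test on change. This part of the reply stands in full.

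A reader might also infer that most significant interactions would end with no pair identified. That holds reliably only for averaged means with two occasions. The objectives speak of efficacy at post-treatment and at 3, 6 and 12 months, so comparison by occasion is at least as natural a reading, and there the shares are much smaller. Raw post-treatment comparisons are unbiased under randomization, which here is stratified by severity. Their loss of power is specific to r = .7: at r = .5 (an assumption) the SD of change is √(2 × 0.5) = 1, and change has no advantage.

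A third inference, that occasion comparisons would get wrong error bars, is not supported. The text never says Tukey is used on occasion means, and the link to homoscedasticity suggests that arm comparisons are meant.

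Finally, the named tests are introduced only as examples, procedures may vary, and a fuller analysis plan may exist. This reply is weaker. Both examples are of the same independent-groups type, and the permission to vary commits to no suitable contrast. The article does not leave the follow-up to another document: it names the procedures and the rule for choosing between them. The promised effect sizes do not close the gap either, since their target is also unstated.

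**Conclusion.** The concern holds in a limited form. The article sizes the trial on the arm-by-occasion interaction and names follow-up tests for it, but does not tie those tests to the matching contrast. Depending on which means are compared, the share of significant interactions with no arm pair identified runs from about 2% to about 80% with two occasions at 49 per arm. With five occasions it runs from under 1% to about 62%. The figures assume compound symmetry at .7, equal variances, complete data and illustrative mean patterns; a lower correlation would narrow the gap between change and raw scores. The named procedures are not invalid in themselves, and no error in occasion comparisons is established. The point deserves correction because the pairwise step answers the trial's main question and the right contrast uses data already collected.

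**What to change.** Replace the follow-up sentence in the Statistical analysis section with wording such as: *A significant arm-by-occasion interaction will be followed by the three pairwise arm contrasts of change from baseline (or of baseline-adjusted means) at post-treatment and at each follow-up, adjusted for the three pairs; Tukey or, under unequal variances, Games-Howell will be applied to the change scores. Any comparison between occasions will use paired, within-person contrasts.*

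Baseline-adjusted means are the safer option if the correlation may be below .7. Their residual SD is √(1 − r²), which is 0.714 at r = .7 and 0.866 at r = .5, against 0.775 and 1 for change.

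The cost is one or two sentences, settled before outcome data are examined. No extra participants, visits or measurements are needed, and the contrasts are standard output of the usual software.
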